### Exclusion criteria

1. Major learning disabilities or medical disorders
2. Taking medications expected to affect behaviour and learning
3. Taking fish oils already, or eating fish > 2 x week

## Selection of schools

School selection will be critical to the efficient conduct of the study. Outline permission for the study has already been given by Senior Executives at Oxfordshire Education Authority, which has a more than sufficient number of primary schools, but if necessary, suitable schools from neighbouring counties of Berkshire and Buckinghamshire will also be considered.

### School Inclusion criteria

- Mainstream local authority primary schools in Oxfordshire, Berkshire and Buckinghamshire
- Educational authority ethics approval
- Agreement of head and participating teachers

### School Exclusion criteria

- Not meeting the inclusion criteria listed above

Subject to the above, each participating school will be carefully identified on the basis of:

- Having at least one teacher with a specific interest in, and responsibility for, supervising and managing suitable children.
- Showing enthusiasm to participate in the study.
- Ensuring that sufficient time, staff and adequate facilities are available for the trial.
- Providing information to all supporting staff members, parents and children involved with the trial.
- Acknowledging and agreeing to conform to the administrative and ethical requirements and responsibilities of the study, including signing-up to Good Clinical Practice and other regulatory documentation.

# STAGE ONE: ENROLMENT

## Screening

Screening based on the results of age 7+ Key Stage I assessments will be performed to assess a child’s possible eligibility for the study.

Parents/carers of eligible children will be provided with information on the study and invited to consent to their child’s participation.Fully informed written proxy consent (and assent) to participate in the study will be required before any baseline assessments are carried out.

## Enrolment/ Baseline Assessments

The following baseline measures will be obtained on participating children:

1. Teacher: Conners Teacher Ratings (CTRS-L) (Conners 1997)
2. Parent: Conners Parent Ratings (CPRS-L) (Conners 1997)

Demographics

Child Sleep Habits Questionnaire (CSHQ) (Owens 2000)

3. Child: Word reading and Recall of digits (British Ability Scale - BAS II) (Elliott, 1997)
Fingerprick blood measures to assess fatty acid status and compliance

Sleep measured objectively by actigraph on a 10% subset.

## Randomisation Process

1. Fully informed written proxy consent
2. Confirmation of eligibility, randomisation and issue of allocated treatment by Centre for Statistics in Medicine, University of Oxford (see later).

# STAGE TWO: TRIAL TREATMENTS

Stage Two of the study is a simple parallel group randomised double-blind controlled trial comparing the effects of active supplementation with Omega-3 (DHA) at a fixed dose (600mg DHA per day) versus taste and colour-matched placebo. DHA or placebo supplements will be supplied in numbered bottles to be delivered once daily to participating children over 16 weeks by teachers (Monday – Friday) and by parents/carers at weekends and during school holidays.

## Active supplementation

The active intervention will consist of 3 x 500 mg capsules per day, each capsule providing 200 mg of DHA as a triglyceride. The liquid fill contains DHASCO®-S oil, derived from the microalgae, *Schizochytrium sp.,* high-oleic sunflower oil, natural mixed tocopherols, ascorbyl palmitate, and rosemary extract (flavouring). The gelatin shell contains glycerin, water, and colouring (carmel, carmine, turmeric).[[3]](#footnote-4)

## Placebo

The placebo will consist of 3 x 500 mg capsules per day containing high-oleic sunflower oil. The dimensions, taste, appearance and colour will be identical to those of the DHA capsules. The shell of the capsule will be the same as the DHA capsule. The liquid fill contains high-oleic sunflower oil, natural mixed tocopherols, ascorbyl palmitat and rosemary extract (flavouring).

## Supply and Labeling

The active supplement and placebo will be supplied in 100 count bottles. Each participant will be required to consume 3 capsules daily (600 mg of DHA). Each bottle will be labeled with a 2-part label. The inner portion contains the protocol number, the participant random allocation number, a place to record the participant’s initials, storage instructions, sponsor and PI’s name and address and an Investigational Product Statement. The outer tear-off portion of the bottle label contains the protocol number, the participant random allocation number and a place to record the participant’s initials.

## Unblinding of Individual Participants During The Trial

Unblinding will be considered only when knowledge of the treatment assignment is deemed essential for the child’s care by their physician or a regulatory body. In general, unblinding of participants during the conduct of the clinical trial is not allowed unless there are compelling medical or safety reasons to do so. The decision to unblind a single case will only be made when knowledge of an individual’s allocated treatment is essential to:

- Enable treatment of severe adverse event/s, or
- Enable administration of another therapy that is contraindicated by the trial treatment.

Where possible, the agreement of the lead investigators ([name] and/or [name]) will be sought before requests for individual unblinding are made.

## Assessment of Compliance with Study Treatment/s

At the end of each child’s participation in the study, a member of the research staff will collect all unused supplements allocated to that child, and a pill count will be conducted and recorded to determine the doses administered. All unused medication collected will be returned to the research centre where they will be retained for the duration of the trial; at the end of the trial they will be collected for destruction.

## Early withdrawal

If a patient wishes to withdraw from trial treatment, all unused medication will be collected and a pill count conducted and recorded. The unused medication will be returned and retained for the duration of the trial; at the end of the trial they will be collected for destruction.

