## Participant Transfer and Withdrawal

In consenting to the trial, participants are consenting to trial treatment, follow-up and data collection. If voluntary withdrawal occurs, the parent/carer will be asked to allow continuation of scheduled evaluations and to complete an end-of-study evaluation. Follow-up of these participants will be continued through the trial.

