### Withdrawal from Trial Intervention

Participants may be withdrawn from the intervention for any of the following reasons:

1. Parent/ carer of the child withdraws consent for treatment.
2. Unacceptable adverse effects.
3. Intercurrent illness preventing further participation.
4. Development of serious disease preventing further participation.
5. Any change in the participants’ condition that justifies the discontinuation of participation in the opinion of parent, teacher or clinician.

If a parent/carer wishes to withdraw a child from the intervention, schools will inform the project administrator who should document the reason. The project coordinator will attempt to contact the parent/carer, explain the importance of remaining in the trial and being followed-up, and request that data be collected as per the trial schedule. Generally, follow-up will continue unless the parent/carer explicitly also withdraws consent for follow-up (see following section).

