## Post-intervention (Stage Two participants only)

Teacher: Conners Teacher Ratings

Estimate of treatment group

Child: Reading test age

Working memory digit span test

Fingerprick blood measures to assess compliance

Estimate of treatment group

The following measures will be collected from parents using Freepost mail services and chased up with telephone calls or visits as required.

Parent: Conners Parent Ratings

Estimate of treatment group

Child Sleep Habits Questionnaire (CSHQ)

Barkley Side Effects Rating Scale (SERS) (Barkley, 1990)

On the same selected subsample, we will again collect sleep measures objectively by actigraphy and derive the CSDI from the sleep diary.

Participants in both stages of the study will be given a 3 month supply of DHA (Life’s DHA, provided by Martek Biosciences Corporation) as a token of thanks for their participation in the study.

In due course, the parents of all participating children will also receive details of the overall study results, as will all participating schools.

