### Side effects scale

Side effects will be measured post-intervention in all children participating in Stage Two using the Barkley Side Effects Rating Scale (SERS) (Barkley 1990). This scale was designed for use in studies of stimulant medication for ADHD-type symptoms. Based on our own and others’ previous studies, negative side effects are not expected from supplementation with DHA, but we are conscious that few studies specifically ask about these effects, so the use of this scale will redress that omission.

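### No side-effect rating is fixed when a child stops capsules early, so the post-intervention scale may understate side effects in the children who stop

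*Protocol*

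**What the plan says.** All references are to the protocol.

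- **Timing of the scale.** Under Side effects scale: "Side effects will be measured post-intervention in all children participating in Stage Two". The schedule agrees. The SERS is among the parent measures under Post-intervention and is absent from the Baseline list. No recall period is stated.
- **Reasons for stopping.** Withdrawal from Trial Intervention lists "Unacceptable adverse effects".
- **What happens at stopping.** Early withdrawal: "If a patient wishes to withdraw from trial treatment, all unused medication will be collected and a pill count conducted and recorded". Withdrawal from Trial Intervention adds that "schools will inform the project administrator who should document the reason", and that the coordinator tries to reach the parent and asks for data collection to continue on the trial schedule.
- **Follow-up after stopping.** Participant Transfer and Withdrawal: "the parent/carer will be asked to allow continuation of scheduled evaluations and to complete an end-of-study evaluation". The timing and content of that last evaluation are not given.
- **Complete withdrawal.** A family may leave without giving a reason. Data up to that point are kept unless the family objects.
- **Missing data.** Loss to Follow-up and Analysis Plan replace missing values by the median of the treatment group.

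**The concern.** Children who stop because of side effects are the ones with most to tell about tolerability. Under the schedule, their only structured rating probably comes at the 16-week follow-up. A child who stopped in week 4 would be rated about 16 − 4 = 12 weeks after the last capsule. If the symptoms have gone by then and the form asks about the present, they are not recorded. If the family has left the trial there is no form. If the median rule were applied to this scale, that child would receive a typical score for the arm.

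The Side effects scale section justifies the SERS by saying that few earlier studies asked specifically about side effects and that this scale will make good the gap. The gap would remain for the group that matters most. A rating not taken near the time of stopping cannot be recovered afterwards.

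**Working it through.** **1. Does another provision close the gap?** No power or sample-size figure in the protocol bears on this, so the first check is of the text.

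| Point in time | What the protocol fixes | Side-effect rating? |
| --- | --- | --- |
| Baseline | Behaviour, reading, memory, blood, sleep, health questionnaire | SERS not listed |
| Stopping early | Capsules collected and counted; reason documented; parent contacted | None named |
| After stopping | Scheduled evaluations, plus an end-of-study evaluation with no stated date | SERS at post-intervention |
| Complete withdrawal | Data to that point kept; no reason required | None |

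Elsewhere, the coordinator checks safety reporting rates between centres (Quality Assurance and Quality Control of Data), the steering committee advises on adverse events, and Pharmacovigilance cites the clinical trials regulations. None of these describes how side effects are collected from a child who stops.

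**2. How large could the effect be?** The only input from the protocol is 180 children per arm. All rates below are assumptions.

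Let c be the proportion affected among children who continue, and s the proportion who stop for side effects.

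- Affected while on capsules: (1 − s)·c + s
- Recorded at week 16 if every stopper is rated and symptom-free: (1 − s)·c
- Loss in the arm difference: s(DHA) − s(placebo)

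With c = 10% in both arms:

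| Stopping, DHA v placebo | On capsules | Difference | Week-16 form | Difference | Loss |
| --- | --- | --- | --- | --- | --- |
| 6% v 1% | 0.94 × 10% + 6% = 15.4% v 0.99 × 10% + 1% = 10.9% | 4.5 points | 9.4% v 9.9% | −0.5 points | 5.0 points |
| 2% v 1% | 0.98 × 10% + 2% = 11.8% v 10.9% | 0.9 points | 9.8% v 9.9% | −0.1 points | 1.0 point |

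In the first row, 15.4% v 10.9% is about 28 v 20 of 180 children, and 9.4% v 9.9% is about 17 v 18. If stoppers are not rated at all, the form shows 10% v 10%.

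**3. Is the direction fixed?** Now let p be the true on-treatment risk, q the share of affected children who stop, and r the share of those whose symptoms have resolved. The recorded risk is p·(1 − q·r). Take p = 20% v 10% and r = 1:

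| q, DHA v placebo | Recorded | Difference | Risk ratio |
| --- | --- | --- | --- |
| 0 v 0 | 20.0% v 10.0% | 10.0 points | 2.00 |
| 10% v 10% | 18.0% v 9.0% | 9.0 points | 2.00 |
| 25% v 25% | 15.0% v 7.5% | 7.5 points | 2.00 |
| 50% v 50% | 10.0% v 5.0% | 5.0 points | 2.00 |
| 50% v 10% | 10.0% v 9.0% | 1.0 point | 1.11 |
| 10% v 25% | 18.0% v 7.5% | 10.5 points | 2.40 |

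With equal q, the difference shrinks and the ratio is unchanged. More stopping among affected children on DHA hides the difference. More on placebo exaggerates it. With equal risks and equal stopping there is no distortion.

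**The case against.** The strongest reply is that stopping for side effects is already recorded. A reader of the Early withdrawal section alone might infer that a pill count is the only thing done at stopping. That is wrong: the reason is to be documented and the parent contacted, so withdrawals for adverse effects can be counted by arm. This stands, and it softens the concern. But a reason for stopping is not the structured rating that every other child receives, and a family that leaves completely need not give one.

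Second, a reader might infer that the arm comparison is biased towards no harm. The protocol does not support that. It would require symptoms that resolve, a form that does not reach back to the time on capsules, and affected children who do not stop more often on placebo. None of these is stated, and the last table row shows the direction reversing.

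Third, week 16 is an inference for children who stop, because the end-of-study evaluation has no date. It is the likely reading, since data are requested on the trial schedule. If an evaluation at stopping was intended, the text should say so.

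Fourth, side effects are not a listed endpoint, the protocol expects none, and tabulation can be left to a statistical analysis plan. All true. But when a form is completed is a matter of data collection, and an analysis plan cannot supply a rating that was never taken. The SERS is the only named scale but not the only safety channel; the oversight provisions simply give no collection procedure.

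Finally, rating every child at one fixed time is a legitimate design. The fix keeps that rating.

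**Conclusion.** The point holds in a limited form. The protocol fixes no side-effect rating at early stopping, only capsule collection, a pill count and a documented reason. A child who stops for adverse effects would probably be rated off capsules, or not at all, so the scale may understate side effects in those who stop.

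The effect on the arm comparison cannot be determined from the protocol. On the assumed rates it runs from about 1 point lost (2% v 1% stopping) to a 4.5-point difference essentially vanishing (6% v 1%). Both figures assume 10% of continuers affected, full resolution by week 16 and a form that does not capture earlier symptoms. Even fully recorded, 15.4% v 10.9% would be detected with a power of only about 24% at 180 per arm (two-sided 5%). The loss is therefore mainly one of descriptive safety information, not of a formal test. The change is worth making because it is cheap and the data cannot be recovered later.

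**What to change.** In Early withdrawal, Withdrawal from Trial Intervention and Side effects scale, state that:

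1. when capsules are stopped for any reason, the parent is asked to complete the SERS at that time, covering the period on capsules;
2. the stopping date is recorded alongside the reason;
3. the scheduled post-intervention form is still completed;
4. the side-effect summary uses the stopping-time form for children who stopped, and stopping for adverse effects is reported by arm.

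Participant Transfer and Withdrawal should also say when the end-of-study evaluation takes place.

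The cost is about a sentence in each section and one extra copy of an existing parent form for the few children who stop, sent when capsules are collected anyway. No visit is added, and no dose or rule for stopping treatment changes.

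There are two limits. The stopping-time forms cover a shorter exposure than the others and are completed just after a decision to stop, so they should be identifiable in the report. Families who withdraw completely may decline the form, so part of the gap will remain.

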## Participant Transfer and Withdrawal

In consenting to the trial, participants are consenting to trial treatment, follow-up and data collection. If voluntary withdrawal occurs, the parent/carer will be asked to allow continuation of scheduled evaluations and to complete an end-of-study evaluation. Follow-up of these participants will be continued through the trial.

### Participant Transfers

Where possible we will aim to screen for these in advance and exclude if the child is known to be moving. If any child does transfer we will attempt to follow him/her up at the new school.

### Withdrawal from Trial Intervention

Participants may be withdrawn from the intervention for any of the following reasons:

1. Parent/ carer of the child withdraws consent for treatment.
2. Unacceptable adverse effects.
3. Intercurrent illness preventing further participation.
4. Development of serious disease preventing further participation.
5. Any change in the participants’ condition that justifies the discontinuation of participation in the opinion of parent, teacher or clinician.

If a parent/carer wishes to withdraw a child from the intervention, schools will inform the project administrator who should document the reason. The project coordinator will attempt to contact the parent/carer, explain the importance of remaining in the trial and being followed-up, and request that data be collected as per the trial schedule. Generally, follow-up will continue unless the parent/carer explicitly also withdraws consent for follow-up (see following section).

### Withdrawal from Trial Completely

Parents/carers are free to withdraw consent at any time without providing a reason. Those who do this will have anonymised data collected up to the point of that withdrawal of consent included in the analyses. The child will no longer receive a daily dose of either active treatment or placebo. Data up to the time of withdrawal will be included in the analyses unless the parent/carer explicitly states that this is not their wish.

## Loss to Follow-up

If any of the trial patients are lost to follow up, contact will initially be attempted through the school and parent address, otherwise missing data will be imputed using median values by treatment group.

# ASSESSMENTS AND PROCEDURES (1) - Overview

Recruitment will be carried out over two years. There will be two assessment points for children in Stage One of the study: screening and baseline. Children in Stage Two of the study will be assessed at three points: screening, baseline and post-intervention.

This section will outline the overall study schedule, the measures that will be administered at each of the assessment points (and by whom), how they will be performed and what will be done with these data.

The following section will provide further details of each of the assessments used.

## Study Schedule

The study will run for 28 months: September 2008 to December 2010. Recruitment for the 16 week intervention will be carried out over two years commencing January 2009 and finishing in July 2010.

NB: The exact study schedule will be planned in detail with participating schools according to term length and any school activities which could interfere with testing sessions (such as examination, sporting or other activities).

Data analysis and write up will be conducted between July and December 2010.

## Screening

Children aged 7-9 years (inclusive) whose Key Stage 1 scores at age 7 years place them within the lowest third for literacy, but whose teachers judge them tohave no other significant learning difficulty.

Research staff will check with the school whether the child meets other eligibility criteria, i.e. has no major learning disabilities or medical disorders

If the child passes this initial school screening stage, teachers will be asked to confirm whether their reading is still a cause for concern. If it is not they will no longer be considered for inclusion in the study. Teachers will be asked to add the names of any additional children whose reading shows room for improvement.

Parents of potential participants will be contacted via a letter from their child’s school briefly describing the study. More detailed participant information will also be mailed with this letter along with a simple version for children, and the consent form and a freepost envelope addressed to their child’s school.

The invitation letter will ask parents to let the school know if they do not wish the school to give the researchers their contact details. Unless parents express a wish not to be contacted, this letter will be followed by a phone call from the researchers in which parents will be given the opportunity to ask questions and discuss the study. If necessary, arrangements will be made to either visit the parents at home or meet them at school.

Parents of children in Stage One of the study will be asked to provide assessments at baseline, and those in Stage Two will be asked to provide these same assessments again post-intervention. It will be made clear to all parents that if their child is chosen to take part in Stage Two of the study they will be asked to give their child supplements each day during weekends and school holidays.

## Baseline

Confirmation that signed consent forms are in the PIs possession is required before baseline visits to schools will be arranged. The following measures will be administered in the school by the research staff:

Teacher: Conners Teacher Ratings

Child: Reading test age

Working memory digit span test

Fingerprick blood measures to assess compliance

At this point assessment measures will be scored by researchers. Children who meet inclusion criteria for Stage Two will be identified and randomization will be performed by telephone.

The following measures will be collected from parents using Freepost mail services and chased up with telephone calls or visits as required.

Parent: Conners Parent Ratings

Health questionnaire

Demographics

Child Sleep Habits Questionnaire (CSHQ)

On a 10% block random selected subsample of Stage Two participants, we will collect sleep measures objectively by actigraphy. This will require a home visit before supplementation begins to provide the actigraph and explain how to use it, and another home visit to collect it 5 days later.

